### Outcome measurements

#### Primary outcomes

##### Visual analog scale (VAS)

We will use the visual analog scale as the primary outcome measure [23]. VAS is one of the sensitive and reliable methods for pain measurement, which is used to evaluate the degree of low back pain. VAS scores ranged from 0 points to 10 points, which were described in detail as follows: 0: painless; less than 3 points: slight pain that can be tolerable; 4–6 points: pain to affect the sleep, which can be tolerated; 7–10 points: gradually intense pain, which is unbearable and affects appetite and sleep.

#### Secondary outcomes

Oswestry disability index (ODI) [24, 25] is one of the most widely used scoring scales for functional outcome evaluation of patients with low back pain, which can be used to evaluate lumbar dysfunction. It consists of 10 questions, including pain intensity, self-care, lifting, walking, sitting, standing, interference with sleep, sexual life, social life, and tourism. A higher score may indicate a more serious dysfunction.

Modified Japanese Orthopaedic Association low back pain (M-JOA) score [26] is a frequently used scale. It includes subjective symptoms (lumbar pain, lower limb radiative pain and numbness), objective symptoms (paravertebral tenderness, muscle tension, Lasegue test, and femoral nerve stretching test), and daily behavior ability (working ability, sleep, bending, and lifting) to evaluate lumbar conditions and activities of daily living. The score ranges from 0 points to 30 points, and a lower score may reveal a milder condition.

Serum β-EP and serum SP will be used to assess the improvement of pain in LDH. Previous clinical studies [27, 28] have reported that the reduction of pain in LDH might be correlated with the levels of serum β-EP and SP, which may be considered as one of the analgesic mechanisms of reducing low back pain in LDH. Methods of detection: At baseline and after the end of treatment, 4ml venous blood samples were collected from patients on an empty stomach in both groups, which were placed in serum separation tubes. Blood samples were then centrifuged at 1000×*g* for 20 min, the supernatant was then collected and stored in a refrigerator at − 80°C for further measurement. Enzyme-linked immunosorbent assay (ELISA) was used for determination, and the operation was carried out in strict accordance with the instructions of the kit. The test is conducted by the Central Laboratory of No.1 Affiliated Hospital of Guizhou University of Traditional Chinese Medicine.

### Concomitant care

From the time of participation in this study to the end of follow-up, it is recommended that patients do not take anti-inflammatory and analgesic drugs or any other non-drug therapy for low back pain, because this may affect the objective evaluation of the efficacy of Ma’s bamboo-based medicinal moxibustion therapy. However, if the patient needs to use other treatment methods other than the treatment plan of this study, patients can apply to the investigator to withdraw from the clinical trial, and any rights and interests of the patient will not be harmed.

### Adherence

Before the start of the trial, the investigators will fully inform the patients of the benefits and the possible inconvenience of the study. MRI of the lumbar vertebrae, laboratory examination, and twelve times of treatment will be free of charge in order to improve the adherence of the patients. The baseline data of each patient (name, gender, age, address, telephone, or contacts of immediate family members) will be recorded in detail, hereby to facilitate the supervision of patients’ adherence. The cases of drop-out, withdrawal, and discontinuation will be recorded and followed up by telephone or even followed up at patients’ homes if necessary.

### Data monitoring and management

Our study group will set up a special data monitoring committee for data management and quality control, which consists of hospitals, company, and institute.

#### Quality control system

All three-level quality monitoring system was established. Clinical research associates (CRAs) were assigned for data monitoring. Level 1 monitoring requires the CRAs in the two hospitals (No. 1 Affiliated Hospital of Guizhou University of Traditional Chinese Medicine, No. 2 Affiliated Hospital of Guizhou University of Traditional Chinese medicine) to monitor the quality of the CRFs once a week, fill out the monitoring report, and report to the principal investigator (PI) in time. Level 2 monitoring requires the CRA from INTELLIGENCE FUTURE Soft Co., Ltd to conduct quality monitoring once every six months, fill out the monitoring report, and report to the project leader of INTELLIGENCE FUTURE in time. Level 3 monitoring requires the person in charge or the technical backbone at the institute of Chinese Medical History and Literature, China Academy of Chinese Medical Sciences to monitor once or twice annually.

#### Data management platform

The data management platform was set up by INTELLIGENCE FUTURE soft Co., Ltd. It includes the IWR and EDC systems. It includes nine modules, including data entry and statistics. All data will be entered using a double-entry procedure performed by two different individuals.

### Consent and assent

The study clinician obtained written consent from the patient. All subjects included in the present clinical study had voluntarily participated, signed an informed consent form (Additional file 2), and received a copy of the informed consent form. Prior to collecting any data, the consent of the patient was sought.

### Confidentiality

All data will be confidential. The CRFs will be stored in a locked filing cabinet in the team office. The data collected by investigator A of each center will be kept confidential by the data analyst and stored in the data management platform. The data management platform access account and password will be known only to Investigator A and data analyst.

### Statistical analysis

Data analysis will be conducted in accordance with the intention-to-treat principle. Missing data will be handled using linear mixed effects models. Statisticians and chief investigators will work out an analysis plan and related forms before the database lock. The analysis will include case distribution, comparison of basic values, compliance, effectiveness, factors that influence efficacy, and safety. Subgroup analysis will be performed according to pathological classification and syndrome classification. Statistical analysis will be conducted using SAS 9.2 (SAS Institute Inc., Cary, NC, USA). The Wilcoxon rank-sum test, *t* test, or variance analysis will be performed for inter-group or intra-group comparison according to data distribution. The Wilcoxon rank-sum test will be used to compare ranked data. The chi-square test will be applied to compare enumeration data. All tests will be one-sided. A *p* value <0.05 will be considered statistically significant.

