#### Pathological classification [16]

Intervertebral disc bulging, with an outward bulge of the annulus fibrosus of the whole intervertebral disc uniformlyLocalized herniation of the intervertebral disc, rupture of the inner layer of annulus fibrosus of the intervertebral disc, and partial herniation of nucleus pulposusIntervertebral disc herniation, rupture of most annulus fibrosus of the intervertebral disc, with intact outer annulus fibrosus merely, and the nucleus pulposus confined to the intervertebral discProlapse of the intervertebral disc, rupture of all annulus fibrosus of the intervertebral disc, nucleus pulposus tissue protruding out of the intervertebral disc and bound by the posterior longitudinal ligamentSequestered disc herniation, nucleus pulposus tissue protruding out of the annulus fibrosus and posterior longitudinal ligament, and sequestered in the spinal canal

Note: In this trial, patients with a pathological classification of intervertebral disc bulging, localized herniation of the intervertebral disc, and intervertebral disc herniation will be selected for experiment according to the long-term treatment experience and practice by using Ma’s bamboo-based medicinal moxibustion therapy.

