#### Syndrome classification [17]

Low back pain due to cold-dampness evil

The presence of a history of suffering from cold in the waist, aggravation of symptoms when the weather changes or when there is cloudy, rainy, or cold weather, with severe cold and pain in the waist, accompanied by numbness or contracture that restricts the body movements of bending or raising up, even with pain involving the lower limbs2.Low back pain due to dampness-heat evil

Severe and heat pain in the waist, aggravation of symptoms in summer-heat and damp, cloudy and rainy weather, and possible alleviation after activities, accompanied by heavy body and feeling of sleepy, short voiding of reddish urine, yellow and greasy fur on the tongue, as well as soft and frequent pulse or wire and frequent pulse3.Low back pain due to static blood

The presence of a history of strain or old injury in the waist, aggravation of symptoms when getting up in the morning, tired and sitting for a long while, with stiffness of the muscles on both sides of the waist, pain like the stabbing of a needle, and pain in a fixed site4.Low back pain due to kidney deficiency

Major manifestations of soreness and weakness, with dull pain, alleviation when pressing and lifting, accompanied by weakness in legs and knees with relief when lying down and repeated onset, with fatigue and hypersomnia, and thready pulse as well

Note: In our study, patients with all the types based on the syndrome classification mentioned above will be included for experiment according to the long-term treatment experience and practice by using Ma’s bamboo-based medicinal moxibustion therapy.

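### The blanket rule of one-sided tests at 0.05 does not fit the planned subgroup analyses by pathological and syndrome class

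*Protocol article*

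**What the plan says.** The *Statistical analysis* section of the protocol article plans subgroups in one sentence: "Subgroup analysis will be performed according to pathological classification and syndrome classification". It lists the t test, the Wilcoxon rank-sum test and variance analysis for comparisons between and within groups. It then closes with a rule for everything: "All tests will be one-sided", and a p "value <0.05 will be considered statistically significant". Subgroup analyses are not excepted.

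The classes are fixed under *Eligibility criteria*. Of the five pathological types listed, three are enrolled: "intervertebral disc bulging, localized herniation of the intervertebral disc, and intervertebral disc herniation will be selected for experiment". Of the four syndrome types, all are enrolled: "patients with all the types based on the syndrome classification mentioned above will be included for experiment". That makes 3 + 4 = 7 classes, and each patient belongs to one of each kind.

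The section also announces a later document: "Statisticians and chief investigators will work out an analysis plan and related forms before the database lock". The article does not say how the subgroups will be tested, or what a class-level result would be used for.

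**The concern.** A subgroup analysis in a two-arm trial asks whether the treatment difference is the same across classes. That question has no favoured direction. A one-sided rule belongs to the primary non-inferiority comparison, where only one direction leads to a claim. Extended to subgroups, it causes two problems.

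- The standard test of the subgroup question cannot be directional when a classification has three or four levels. A reader who follows the rule to the letter is steered towards directional two-arm comparisons inside each class, which do not answer the question. One class being significant and another not is no evidence that they differ.
- A one-sided superiority test inside a class treats a class in which moxibustion does worse in the same way as a class with no difference. Both are merely not significant. Finding a class that does worse is one of the main reasons to look at subgroups.

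At stake is a wrong statement about which type of patient does better or worse with moxibustion than with acupuncture. The primary conclusion is not affected.

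**Working it through.** **Inputs.** From *Sample size calculation*: SD 2.0, margin 0.78, one-sided 0.05, power 90%, 140 evaluable per group, 156 randomised per group after 10% loss. From *Eligibility criteria*: 3 and 4 classes. From *Statistical analysis*: one-sided, 0.05. The article gives no class shares, so equal shares are assumed unless stated otherwise.

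**The plan's own figure.** No subgroup error rate is stated, so there is none to reproduce. The stated sample size is used below only to size the classes. With n = 2(z₁₋α + z₁₋β)²SD²/margin² and no true difference:
- one-sided 0.05: 2 × (1.645 + 1.282)² × 4 / 0.6084 = 112.7, so 113 per group (114 by the t distribution);
- one-sided 0.025: 2 × (1.960 + 1.282)² × 4 / 0.6084 = 138.2, so 139 (140 by t), and 140/0.9 = 155.6, so 156.

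The stated 140 therefore matches one-sided 0.025 and not the stated 0.05. That is a separate matter. It hardly touches the present point, because the false-positive figures in step 3 barely depend on the sample size.

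**Step 1: does the interaction test have a direction?** Degrees of freedom are (arms − 1) × (classes − 1): 1 × 2 = 2 for pathological class and 1 × 3 = 3 for syndrome class. With more than one degree of freedom the test is an omnibus F or chi-square test. It rejects for any pattern of differences. It uses the upper tail of its own distribution, but that is not a directional hypothesis. The words one-sided therefore have no meaning for it.

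**Step 2: what does a one-sided test inside a class show?** With equal shares a syndrome class has 140/4 = 35 per arm, and the standard error of the difference is 2.0 × √(2/35) = 0.478. Suppose moxibustion is observed to be worse by the full 0.78. Then z = −0.78/0.478 = −1.63 and the one-sided superiority p value is about 0.95. An observed difference of zero gives p = 0.50. Both are reported as not significant. A one-sided non-inferiority test would fail to show non-inferiority in the first case, but such a failure does not show that moxibustion is worse.

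**Step 3: if separate superiority tests were run in all seven classes, with no true difference in any class.**
- Three pathological classes alone: 1 − 0.95³ = 14.3%.
- Four syndrome classes alone: 1 − 0.95⁴ = 18.5%.
- All seven as if independent: 1 − 0.95⁷ = 30.2%.

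The two classifications cover the same patients, so the seven tests are correlated and the true figure lies below 30.2%. Simulated with 40,000 runs per scenario and unrelated classifications, it is 26.7% (280 patients, equal shares), 26.5% (312, equal), 26.5% (280, unequal) and 26.7% (280, very unequal). A smaller simulation of 6,000 runs gave 25.8%. For comparison, one interaction test per classification at 0.05 gives 1 − 0.95² = 9.8% if the two are independent.

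**Step 4: how much can one class support?** The half-width of a two-sided 95% interval is 1.96 × 0.478 = 0.94 in a syndrome class. In a pathological class (140/3 = 46.7 per arm, standard error 2.0 × √(2/46.7) = 0.414) it is 1.96 × 0.414 = 0.81. Both exceed 0.78, so even an observed difference of exactly zero would leave the margin inside the interval. At one-sided 0.05 with equal treatments, the power to show non-inferiority within a class is about 49% (35 per arm) and 59% (about 47 per arm). This is ordinary for a trial sized on its overall comparison. It is a reason to make no claim within a class.

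**The case against.** The strongest objection is that the article leaves the subgroup method open. It does not say that each class will be tested separately, and it does not rule out an interaction term. Variance analysis can carry one, and the same section lists factors that influence efficacy among the planned analyses. The choice between interaction and within-class tests, the handling of multiplicity and the exploratory label are commonly left to the analysis plan, which the section announces. Their absence from a condensed article is not an error.

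All of that stands, and it rules out several stronger readings that a reader might infer:
- That the plan prescribes seven separate tests. It does not, so the figures in step 3 are conditional.
- That the 26–30% is the chance of a false finding that the therapy works in some type. It is the chance of a false finding of superiority over acupuncture. For non-inferiority tests it would apply only if moxibustion were worse by exactly 0.78 in every class. With equal treatments, a class that shows non-inferiority is a correct result.
- That one-sidedness inflates the error. The number of tests does that; one-sidedness only puts the whole 0.05 in one direction.
- That subgroup results will decide who is offered the therapy. The classifications are used for trial entry, and nothing says that subgroup results will guide treatment.

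What survives is what the article states: every test is one-sided at 0.05, with no exception. An analysis plan that follows the article inherits that rule. *Protocol amendments* says that the analyses stay as they are after first enrolment, which was in November 2020, and sends significant analysis changes to the ethics committee. Filling in an open method is no modification, but departing from a stated rule should be explicit. The same sentence also governs the secondary, baseline and safety comparisons, so this point can be settled together with any general correction of it.

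**Conclusion.** The concern holds in a limited form, and it is minor. A rule that makes every test one-sided at 0.05 is badly fixed for subgroup analyses over three pathological and four syndrome classes. It cannot be applied to a treatment-by-class test with 2 or 3 degrees of freedom, and inside a class a one-sided superiority test cannot reveal that moxibustion is worse. This rests on the text alone and needs no assumption about class sizes.

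The numerical consequence is conditional. It assumes separate within-class tests for superiority, no true difference in any class, and unrelated classifications. The chance of at least one false result of better than acupuncture is then about 26–27%, with 30% under independence. Different class shares and sample sizes hardly changed it. The article does not commit the trial to that procedure, so the figure shows what to avoid and does not measure an error already made.

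**What to change.** In *Statistical analysis*, exempt the subgroup analyses from the one-sided rule. State that:
- each classification will be examined by a treatment-by-class interaction test, an omnibus test and not one-sided, in the model used to analyse VAS;
- the difference between arms will be reported in each class with a two-sided 95% confidence interval;
- these results are exploratory, with no claim of significance or non-inferiority within a class.

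The article mentions linear mixed effects models only for missing data, so the VAS model has to be named when this is written; it should not be taken as already described.

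The cost is a few lines of wording and one interaction term per classification. It needs no new data and no extra patients. Whether the change goes into the announced analysis plan or through an amendment should follow the article's own amendment procedure.

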## Methods

### Study design and setting

This is a parallel, non-inferiority, randomized controlled clinical trial aiming to compare the effect of Ma’s bamboo-based medicinal moxibustion therapy and regular acupuncture therapy on low back pain in LDH patients. The patients will be enrolled among outpatients and inpatients from the acupuncture departments of No.1 Affiliated Hospital of Guizhou University of Traditional Chinese Medicine, No.2 Affiliated Hospital of Guizhou University of Traditional Chinese medicine. Eligible patients will be randomly assigned to a Ma’s bamboo-based medicinal moxibustion therapy group and an acupuncture group in a 1:1 ratio. All items from the World Health Organization Trial Registration Data Set are shown in Table 1. The study flowchart is provided in Fig. 1. A Standard Protocol Items: Recommendations for Interventional Trials (SPIRIT) checklist and figure are provided respectively in Additional file 1 and Fig. 2.

**Table 1 Tab1:** All items from the World Health Organization Trial Registration Data Set (SPIRIT checklist, item 2b)

Data category	Information
Primary registry and trial identifying number	http://www.chictr.org.cn; ChiCTR2000038725
Date of registration in primary registry	29 September 2020
Secondary identifying numbers	-
Source(s) of monetary or material support	National Key Research and Development Project of China (2019YFC1708403)
Primary sponsor	Institute of Chinese Medical History and Literature, China Academy of Chinese Medical Sciences
Secondary sponsor(s)	-
Contact for public queries	[name]; [contact]
Contact for scientific queries	[name], Guizhou University of Traditional Chinese Medicine, [name], China.
Public title	Folk diagnosis and treatment technology in lumbar disc herniation study
Scientific title	Ma’s bamboo-based medicinal moxibustion therapy of low back pain in lumbar disc herniation: study protocol for a randomized controlled trial
Countries of recruitment	China
Health condition(s) or problem(s) studied	Lumbar disc herniation, low back pain
Intervention(s)	Ma’s bamboo-based medicinal moxibustion group

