### Sample size calculation

The PASS software version 15.0 (NCSS, LLC. Kaysville, UT, USA.) was used to estimate the sample size. The trial is designed to determine the efficacy of Ma’s bamboo-based medicinal moxibustion therapy on low back pain in LDH and prove that its clinical efficacy is not inferior to normal acupuncture therapy. Therefore, we chose a non-inferiority trial design. According to the previous literature [8, 18] and the joint consideration of clinicians and statisticians, it is assumed that the standard deviation of VAS score reduction of patients using bamboo-based medicinal moxibustion is 2.0, the non-inferiority margin was set at 0.78, the significance level of the test is unilateral 0.05 and power of the test is 90%. According to the 1:1 grouping, the sample size required by each group was 140 cases, and the lost follow-up rate will be estimated at 10%. The final sample size of the treatment group and the control group was 156 cases respectively, and the total sample size was 312 cases.

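### The trial is sized for non-inferiority with a margin of 0.78 on VAS reduction, but the analysis section ties none of its tests to that margin

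*Protocol article*

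**What the plan says.** The design is stated plainly under Study design and setting: "This is a parallel, non-inferiority, randomized controlled clinical trial". Sample size calculation repeats it ("we chose a non-inferiority trial design") and gives the inputs: "the non-inferiority margin was set at 0.78", with a "standard deviation of VAS score reduction of patients using bamboo-based medicinal moxibustion is 2.0", and "the significance level of the test is unilateral 0.05 and power of the test is 90" per cent. From these, "the sample size required by each group was 140 cases", raised to 156 for 10% loss.

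The Statistical analysis section names its between-group methods as the Wilcoxon rank-sum test, the t test or ANOVA: "variance analysis will be performed for inter-group or intra-group comparison according to data distribution". It adds that all tests are one-sided and that p below 0.05 counts as significant. The analysis follows intention to treat, and linear mixed models are named, but only for handling missing data. An analysis plan is to be written before database lock.

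The figure 0.78 appears in the sample size section and nowhere else in the article.

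**The concern.** A non-inferiority conclusion needs a null hypothesis placed at the margin, or equivalently a confidence limit compared with the margin. The analysis section supplies neither. A reader who runs the listed tests in their usual form tests a difference of zero, which is a different question from the one the trial was sized to answer.

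Choosing the test by distribution loosens the link further. The margin and the SD are on the scale of mean VAS reduction. A standard rank-sum test gives no estimate on that scale, and an ANOVA F test has no direction, so it does not by itself deliver the one-sided test that the section requires. Whether the primary result can be set against 0.78 at all would then depend on how the data look.

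At stake is the main conclusion. If the arms perform alike, which is a success for this design, tests against zero would usually be non-significant. The article would then give no stated basis for claiming non-inferiority or for refusing the claim.

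**Working it through.** **Inputs.** Margin 0.78, SD 2.0, one-sided alpha 0.05, power 90%, 1:1 allocation, 140 evaluable and 156 randomised per group, 10% loss (all from Sample size calculation). Two assumptions are added. The true difference is 0, which is not stated. The SD of 2.0 applies to both arms; the article gives it for moxibustion only.

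**1. The plan's own sample size.** n per group = 2 × SD² × (z_alpha + z_power)² / margin².

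- One-sided 0.05: 2 × 4 × (1.645 + 1.282)² / 0.6084 = 112.6, so 113 (114 with the t distribution). After 10% loss: 126 to 127.
- One-sided 0.025: 2 × 4 × (1.960 + 1.282)² / 0.6084 = 138.2, so 139 (140 with the t distribution). After loss: 140 / 0.9 = 155.6, so 156.

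The stated 140 and 156 are not reproduced at the stated alpha of 0.05. They are reproduced at one-sided 0.025. In either case the size comes from a test against 0.78.

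**2. Standard error.** SE = 2.0 × √(2/140) = 0.239.

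**3. Chance of success when the arms are truly equal (noncentral t).**

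| Test | 140 per group | 156 per group |
|---|---|---|
| Against the margin, one-sided 0.05 | 94.6% | 96.3% |
| Against the margin, one-sided 0.025 | 90.2% | 93.0% |
| Against zero, favouring moxibustion, one-sided 0.05 | 5% | 5% |

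**4. The same contrast as an observed result.** With 140 per group, the critical t times the SE is 0.395 at one-sided 0.05. A test against the margin succeeds if moxibustion's observed deficit is below 0.78 − 0.395 = 0.385. A test against zero succeeds only if moxibustion's observed advantage exceeds 0.395. Results between these two points are non-inferior under one reading and non-significant under the other.

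**5. Non-significance read as non-inferiority, with a true deficit of exactly 0.78.** This uses the stated one-sided 0.05.

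- Test looking for moxibustion being worse, 140 per group: Φ(1.645 − 0.78/0.239) = Φ(−1.62) = 5.3% (5.4% with noncentral t).
- Same test, 156 per group: about 3.7% (noncentral t).
- Same test, 100 per group: SE = 2.0 × √(2/100) = 0.283; Φ(1.645 − 0.78/0.283) = 13%.
- Test looking for moxibustion being better, 140 per group: Φ(1.645 + 3.26), which is almost 100%.

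The direction decides the answer, and the article does not state it.

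**The case against.** The best defence is that this is detail deferred to the analysis plan. The article condenses a longer document, announces that plan, and offers the quoted sentence as a general list covering every outcome and comparisons both between and within groups. A shifted null or an interval rule is ordinary content for an analysis plan.

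Part of this stands: the later plan may supply the rule, and its absence from an article would not by itself be a fault. But the article does state tests and a significance rule, and they are not connected to its own design. The Protocol amendments section also says that analyses will not be modified after the first enrolment, which Trial status puts in November 2020, before this article. The same section does allow significant changes with ethics approval, so the route to a correction is open.

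A reader might infer that the named tests cannot establish non-inferiority. The documents do not support that. A t test can be run against a null shifted by the margin, and the one-sided wording is compatible with such an intention. A significant one-sided result favouring moxibustion would also imply non-inferiority. What is missing is the shift, the direction or the limit.

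A reader might also infer that a non-significant result will be taken as proof, with a much inflated error rate. No section proposes this. A two-sided 0.05 test would pass a true deficit of 0.78 about 10% of the time, but the article states one-sided tests. At the stated level, looking for inferiority, the figure is about 5% at the planned size. The 13% needs 100 evaluable per group, a loss of 56 of 156 (36%), against the planned 10%. The practice would still be invalid in principle, but these figures do not show gross inflation at the planned size.

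**Conclusion.** The point holds as a mismatch between a stated design and stated tests. The trial is designed and sized to exclude a deficit of 0.78 in mean VAS reduction, and the analysis section never uses that number. Choosing among rank-sum, t test and ANOVA by distribution makes the connection weaker still.

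With truly equal arms and 140 per group, the chance of a successful result is about 95% if the test is placed at the margin (one-sided 0.05) and 5% if it is placed at zero in favour of moxibustion. These figures rest on an SD of 2.0 in both arms, a true difference of zero and approximately normal means.

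This should be corrected before unblinding, because the central conclusion has no stated decision rule. The conclusion does not extend to saying that the trial cannot show non-inferiority, or that the sponsor intends to read non-significance as success.

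**What to change.** State one primary rule, through the amendment route that the protocol already provides and before unblinding:

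- Name one VAS time point as primary. The abstract lists three assessments after baseline (after six treatments, end of treatment, follow-up).
- Define the difference as mean VAS reduction with acupuncture minus mean VAS reduction with moxibustion, so that a positive value means moxibustion is worse.
- Set the null hypothesis as a difference of 0.78 or more. Estimate the difference from the linear mixed model already named, and conclude non-inferiority only if the upper confidence limit is below 0.78.
- Apply this rule whatever the distribution. Keep the rank-sum test as a sensitivity analysis of difference only.
- Reconcile the confidence level with alpha. One-sided 0.05, as stated in both sections, corresponds to a two-sided 90% interval. The stated 140 per group matches one-sided 0.025, a two-sided 95% interval. Choose one and make the sample size and analysis sections agree. With 140 per group, power is about 95% under the first and 90% under the second, so neither choice needs more patients.

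The cost is a few sentences in the protocol and the analysis plan, plus ethics approval of the amendment. No data collection changes.
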